### Definitions of covariates

Differences in patient demographics (age and biological sex) and characteristics (body mass index (BMI), smoking status and alcohol consumption) between those anticoagulated for AF and those not anticoagulated will be described for each period. Differences in the stroke risk score (Congestive heart failure, hypertension, age ≥ 75 (doubled), diabetes mellitus, stroke (doubled), vascular disease, age 65-74, sex category (female) (CHA_2_DS_2_-VASc))^17^ and the bleeding risk score (Hypertension, abnormal renal or hepatic function, stroke, bleeding, labile INRs, elderly, drugs or alcohol (HAS-BLED)),^18^ comorbidities and concomitant medication will also be described. These covariates are defined in the following subsections.

#### ​CHA_2_DS_2_-VASc score

International guidelines recommend using this score to calculate stroke risk in patients with AF.^3–5^ Higher scores indicate an increasing risk of stroke and the maximum score is 9. Definitions for each element were based on those described by Lip and colleagues^17^ but have been modified for clarity:

*Congestive heart failure (1 point*): right or left ventricular failure or heart failure. Supportive information includes Read codes for heart failure clinic attendance or referral, heart failure monitoring or reference to heart failure therapy/education.

*Hypertension (1 point*): primary or secondary hypertension or hypertensive disease states, for example, hypertensive heart disease. Supportive information includes codes for monitoring, referral to specialist clinics or reference to therapy for hypertension.

*Age≥75 (2 points*).
*Diabetes mellitus (1 point*): type 1 or type 2 diabetes mellitus diagnosis or the consequences of diabetes mellitus, for example, diabetic retinopathy. This also includes anyone prescribed oral hypoglycaemic agents and/or insulin, and excludes gestational diabetes and steroid-induced diabetes as these are often reversible. Supportive information includes dietary advice, reference to diabetes therapies, referral to specialist clinics or educational programme.

*Stroke/transient ischaemic attack or thromboembolism (2 points*): stroke includes ischaemic stroke transient ischaemic attacks and excludes haemorrhagic stroke and venous infarctions. Thromboembolism includes arterial embolic disease and surgeries to treat arterial emboli, and excludes thrombosis and venous embolic disease, which are included in vascular disease.

*Vascular disease (1 point*): includes coronary artery disease (prior myocardial infarction, angina pectoris, percutaneous coronary intervention or coronary bypass surgery and aortic plaque); peripheral vascular disease (intermittent claudication, previous surgery or percutaneous intervention on the abdominal aorta, bifurcation or the lower extremity vessels (limited to surgery on the femoral, popliteal, peroneal and iliac arteries)); and arterial and venous thrombosis and excludes thromboses related to pregnancy.

*Age 64–74 (1 point*).
*Female sex (score 1*).

#### ​HAS-BLED

International guidelines recommend using this score to assess the risk of bleeding with anticoagulants.^3–5^ Higher scores indicate an increased risk of bleeding with anticoagulants. The presence of each disease scores one point and the maximum score is 9. For the purpose of this study, the maximum score for the HAS-BLED will be 8. The L in HAS-BLED corresponds to labile INR defined as a time in therapeutic range with warfarin of less than 60%. As INRs are not recorded consistently in the CPRD and because people prescribed DOACs would not have INR tests at all, this element of the score will not be included. Definitions for each element were based on those described by Pisters and colleagues^18^ but have been adapted to suit the information recorded in the CPRD.

*Hypertension (1 point*): as described for CHA_2_DS_2_-VASc score previously.

*Abnormal renal or hepatic function (1 point each, maximum of 2 points*): renal and hepatic function will be determined using a combination of clinical Read codes and test results.Renal impairment: includes chronic dialysis, transplant and chronic renal impairment (defined as stage 3 or above, moderate, severe or end stage). If renal impairment is recorded with no severity but there is a test result for creatinine of ≥200 µmol/L, the patient will be allocated a point. If there are no test results recorded, the patient will score 0. Codes for renal disease where it does not state that renal function is impaired will be excluded.Hepatic disease: includes chronic hepatic disease (cirrhosis, hepatitis, fatty liver and fibrosis), liver transplantation or biochemical evidence of significant hepatic derangement (bilirubin>2× upper limit of normal in association with aspartate aminotransferase/alanine aminotransferase/alkaline phosphatase) where these blood test results are recorded in CPRD.
*Stroke (1 point*): as described for CHA_2_DS_2_-VASc score previously.

*Bleeding history or predisposition (1 point*): includes any previous bleed; categorised based on the International Society of Thrombosis and Haemostasis guidance as major bleeding where the bleed occurs in a critical area or organ or requires a blood transfusion (CPRD does not state the number of units infused, so any requirement for a blood transfusion in conjunction with a Read code for bleeding will be classified as a major bleed)^19^; or clinically relevant non-major bleeding (defined as a bleed not fitting the major bleed criteria but requiring review by a healthcare professional, as the codes are recorded by a GP we will assume that these bleeds required review)^20^; excludes codes for traumatic bleeding, bleeding related to pregnancy and postoperative bleeding. Predisposition to bleeding includes anaemia and gastric, duodenal and peptic ulcers.

*Elderly (1 point*): defined as being aged >65 years old.

*Drugs or alcohol (1 point each, maximum of 2 points*): a point will be allocated where a patient receives a prescription for an antiplatelet or non-steroidal anti-inflammatory medication within the time period. Exact alcohol consumption is not well documented in the CPRD, but patients will score a point for this element if they have any record stating the number of units consumed per week as >8 units or if they have any codes for heavy/problem drinking.

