## Introduction

A large body of evidence has shown that vitamin K antagonists (VKAs) are safe and effective for stroke prevention in atrial fibrillation (AF), but they have frequently been underused in older people.^1^ Reasons cited by physicians as making them less likely to prescribe VKAs for a person with AF include advancing age, risk of falls, comorbidities and previous bleeding.^2^

The first direct oral anticoagulant (DOAC), dabigatran, was marketed throughout Europe and in the UK in 2008, but was not licensed for stroke prevention in AF until 2011. Since then, three additional DOACs have been licensed for prevention of stroke: rivaroxaban, apixaban and edoxaban, and these are recommended in national and international guidelines as an alternative to warfarin.^3–5^ In the UK, the National Institute of Clinical Excellence (NICE) produces technology appraisals making recommendations for new medicines. The National Health Service is legally obliged to fund those medicines recommended by NICE within 3 months of publication of the appraisal. NICE published favourable technology appraisals for dabigatran and rivaroxaban in 2012,^6 7^ apixaban in 2013^8^ and edoxaban in 2015,^9^ meaning DOACs were available across the UK from mid-2012 onwards for stroke prevention in AF.

DOACs may allay some prescribers’ concerns when deciding whether to anticoagulate their older patients: they have fixed dosing schedules and can be added to compliance aids. They have also been shown in clinical trials to have a significantly lower risk of intracranial haemorrhage than warfarin^10–13^ (a prominent concern in patients with a history of falls).^14^

Since the introduction of DOACs, the overall rate of oral anticoagulant (OAC) initiation has increased by 58%.^15^ However, it is not known whether the introduction of DOACs has changed the rates of OAC prescribing for older people (aged ≥75 years) or how patient demographics, comorbidities and concomitant prescribing affect the choice of anticoagulant prescribed in UK general practice.

This study aimed to characterise prescribing of OACs to people aged ≥75 years in UK general practice, before and after the introduction of DOACs.

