#### ​Previous bleed

Previous bleed includes any non-traumatic bleeding or haemorrhage. Bleeds will be divided in to subsections of major bleeding and clinically relevant non major bleeding (as described in HAS-BLED section), and also by site of bleed (intracranial bleeds, gastrointestinal bleeds or others).

#### 
*​*Dementia

Dementia include dementia (any type), Alzheimer’s disease and anyone prescribed an acetylcholinesterase inhibitor or memantine and excludes cognitive impairment where there is no diagnosis of dementia.

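### HAS-BLED gives no stroke point for haemorrhagic stroke because it borrows the CHA2DS2-VASc definition, and intracranial bleeds coded as traumatic enter no bleeding measure

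*Protocol article*

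**What the plan says.** Four parts of the protocol article bear on this.

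- **HAS-BLED, stroke item.** There is no separate definition: "Stroke (1 point*): as described for CHA_2_DS_2_-VASc score previously".
- **CHA2DS2-VASc score, stroke item.** The definition taken over reads: "stroke includes ischaemic stroke transient ischaemic attacks and excludes haemorrhagic stroke and venous infarctions".
- **HAS-BLED, bleeding history or predisposition.** One point is given for any earlier bleed. The major category is "major bleeding where the bleed occurs in a critical area or organ or requires a blood transfusion". The item "excludes codes for traumatic bleeding, bleeding related to pregnancy and postoperative bleeding". Anaemia and ulcers also earn this single point.
- **Previous bleed (a covariate in its own right).** "Previous bleed includes any non-traumatic bleeding or haemorrhage". Bleeds are split by severity and "also by site of bleed (intracranial bleeds, gastrointestinal bleeds or others").

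The Introduction notes the lower risk of intracranial haemorrhage with DOACs than with warfarin and calls this haemorrhage "a prominent concern in patients with a history of falls". Under objective 3, the mean HAS-BLED score and the proportion with each comorbidity are described by period for patients started on an OAC and for those not started.

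**The concern.** There are two separate gaps.

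First, the haemorrhagic-stroke exclusion was written for a score of stroke risk, where it has an obvious purpose. The cross-reference carries it, without comment, into a score of bleeding risk, where a past brain haemorrhage is plainly relevant.

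Second, the traumatic-bleed exclusion operates in both places where bleeding is measured. An intracranial bleed after a fall, if coded as traumatic, earns neither a stroke point nor a bleeding point, and it is absent from the intracranial row of the Previous bleed covariate. The falls covariate may record the fall, but not the bleed.

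The section on covariate classification says the study wants to learn whether comorbidities influence OAC prescribing. An intracranial bleed after a fall is a natural candidate, given how the Introduction sets out the problem. If it is not recorded, objective 3 cannot show an association with not prescribing. Covariates found important under objective 3 also enter the Cox model of objective 4, and the Discussion expects the results to inform the choice of confounders in later comparative studies. An omission here can therefore carry forward.

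**Working it through.** **1. The plan's own figure.** The HAS-BLED section states a maximum of 8 once labile INR is removed. The item points are hypertension 1, abnormal renal or hepatic function 2, stroke 1, bleeding 1, elderly 1, drugs or alcohol 2.

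1 + 2 + 1 + 1 + 1 + 2 = 8, and 9 with labile INR. The stated maximum reproduces.

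**2. Scoring single events.** Take a patient aged 75 or over with no other risk factor. E is the elderly point, S the stroke point and B the bleeding point. The last column lets haemorrhagic stroke earn S and, for illustration, lets a traumatic intracranial bleed earn B.

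| Past event | As written | If the exclusions did not apply |
|---|---|---|
| None | E = 1 | 1 |
| Ischaemic stroke | E + S = 2 | 2 |
| Haemorrhagic stroke | E + B = 2 | E + S + B = 3 |
| Intracranial bleed coded as traumatic | E = 1 | E + B = 2 |

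Haemorrhagic stroke loses one point. A traumatic intracranial bleed scores the same as no event at all. The maximum of 8 is unchanged either way.

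**3. Effect of the cap on the bleeding item.** That item is worth 1 point at most and is also earned by anaemia. In a patient with anaemia (E + B = 2), a haemorrhagic stroke adds nothing as written and the score stays at 2. An ischaemic stroke raises it to E + B + S = 3.

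**4. Where each event is reported.**

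| Past event | HAS-BLED stroke | HAS-BLED bleeding | Previous bleed, intracranial row |
|---|---|---|---|
| Haemorrhagic stroke, non-traumatic | no | yes | yes |
| Intracranial bleed coded as traumatic | no | no | no |

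The bleeding item does not name the brain as a critical organ. However, any earlier bleed scores, and intracranial is one of the protocol's own bleed sites, so the two entries of yes are secure.

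**5. Effect on the mean score.** Let p be the share of a group with a haemorrhagic stroke and no other event that earns the stroke point. Counting haemorrhagic stroke raises that group's mean by 1 × p. The document gives no value for p. Over an assumed range:

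- p = 1%: 1 × 0.01 = 0.01 points
- p = 2%: 1 × 0.02 = 0.02 points
- p = 5%: 1 × 0.05 = 0.05 points

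The difference in means between two groups moves by the difference in their shares. If both lie within 1% to 5%, that is at most 0.05 − 0.01 = 0.04 points. The share of intracranial bleeds coded as traumatic is not given either, so no figure can be put on the shortfall in the intracranial row.

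**The case against.** The strongest defence is that the scheme is coherent: ischaemic events sit under stroke and haemorrhagic events under bleeding, so one haemorrhage is not counted twice. The HAS-BLED section also says its definitions were adapted to what CPRD records. The first part stands as a possible rationale, but the article does not give it, and a bare cross-reference does not show that the split was intended. Data limits do not explain it, because the Previous bleed covariate already requires intracranial bleeds to be identified.

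On traumatic bleeding, the exclusion is explicit and the same in both places, so there is no contradiction. It also works on codes: a subdural haematoma recorded without a trauma code would still count. Both points are right. They limit the gap to bleeds coded as traumatic, but do not close it. The falls covariate records falls and concern about falls, which covers part of the prescriber's reasoning, but it does not record that a bleed occurred.

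The use is descriptive, and the intracranial row is visible whatever the composite score does. That holds for non-traumatic bleeds only.

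A reader might infer more than the document supports:

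- **That the bleeding measures miss intracranial haemorrhage.** They do not. Non-traumatic cases, including haemorrhagic stroke, keep the bleeding point and their own row.
- **That the Introduction names this as prescribers' main concern.** It speaks of a prominent concern in patients who fall, and lists other reasons for not prescribing without ranking them.
- **That TIA or arterial embolism should not earn the HAS-BLED stroke point.** That rests on the cited source of the score, which is not at hand. The document gives no ground for removing them.
- **That the bleeding-risk contrast is reversed, or the intracranial proportion halved.** Neither can be derived without prevalences that the document does not give.

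**Conclusion.** The point holds in limited form. By cross-reference, a past haemorrhagic stroke is under-scored by 1 of 8 points in HAS-BLED; it is not lost. An intracranial bleed coded as traumatic is lost from every bleeding measure, so objective 3 cannot show whether it is linked to not prescribing.

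The effect on the mean score is probably small: 0.01 to 0.05 points, on the assumption that 1% to 5% of patients have a haemorrhagic stroke and no other event that earns the stroke point. The more important consequence is the incomplete intracranial-bleed comparison. Its size depends on how often such bleeds carry a trauma code, which the document does not say. This is a worthwhile, inexpensive improvement to covariate definitions and does not threaten the study's main descriptive results.

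**What to change.** 1. In the HAS-BLED section, replace the cross-reference with a stroke definition specific to that score, so that the haemorrhagic-stroke exclusion does not carry over. If one event earning both the stroke and the bleeding point is a concern, report the mean score with and without this change.
2. In the Previous bleed section, add a separate row for intracranial bleeds coded as traumatic. Keep the exclusion of all other traumatic bleeding.

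The cost is some extra Read-code list work and a few lines of text. No new data are needed: the plan already has to tell haemorrhagic from ischaemic stroke and traumatic from non-traumatic bleeding in order to apply its exclusions. The one drawback is that a single haemorrhagic stroke may then earn two points, which reporting both versions makes visible.

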### Source population

The study period will start on 1 January 2003 and will end on 27 December 2017. The source population will consist of all patients in CPRD who have ≥1 Read codes for AF and have contributed a minimum of 12 months’ research standard data prior to entry into the cohort. To be eligible to join the study, patients need to have the following: a Read code for AF recorded during or any time prior to the start of the study period; evidence to support the diagnosis of AF, such as a second AF diagnosis at a later date, an echocardiogram or prescription for a rate limiting or antiarrhythmic medication in the 3 months before the AF diagnosis or anytime after; and age of ≥75 years at study entry.

Patients will enter the cohort at the latest of the following dates:

Start of the study period.First AF diagnosis.75th birthday.A year from the date they started to contribute research standard data.

Patients will be censored if they leave the practice, the practice stops contributing data, at their date of death or at the end of the study. For the incidence calculations and comparison of patient characteristics, patients will be censored when they are prescribed an OAC.

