### Covariate classification

It is recognised that some patients may remain in the cohort for a long time and their covariates may change. Therefore, covariates will be identified separately for each of the time periods the patient contributes data and will be grouped by DOAC, warfarin or no OAC, depending on exposure for that period.

We want to investigate whether certain comorbidities influence the prescribing of OACs. We will therefore look for comorbidities accumulated up to the end of the time period for patients who do not receive an OAC or the OAC index date where one is prescribed. Patients will be classified as having a comorbidity if the patient record contains ≥1 diagnostic Read code for a disease or ≥3 Read codes supporting the presence of the disease at any time prior to the relevant date for that period. Read codes used to support the presence of disease include attendance at specialist clinics (eg, diabetes clinics) or codes related to follow-up, such as hypertension monitoring.

Concomitant medication will be classified as≥1 prescription issues for a medication of interest in the 3 months prior to study entry, commencing an OAC, or the end of the time period. We will describe medications at study entry as baseline and then in each time period for the no OAC and incident OAC patients as described for the comorbidities previously mentioned. The medications of interest affect either stroke or bleeding risk or commonly interact with OACs (antihypertensives, antiplatelets, statins, diabetic medications, antiarrhythmics, non-steroidal anti-inflammatory drugs, corticosteroids, anticonvulsants, systemic azoles, HIV protease inhibitors and ciclosporin).

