#### ​Renal impairment

DOACs are predominantly renally cleared and so require dose adjustment and careful monitoring in renal impairment. The elimination of warfarin is mostly metabolic, being metabolised by hepatic enzymes so it is not affected by changes in renal function. Renal impairment may therefore affect the decision of which anticoagulant (if any) to use so it has been included as a covariate alone, in addition to its inclusion in the HAS-BLED score. The Read code or test result dated closest to the relevant date for the period will be used to categorise the presence and level of renal impairment.

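### The HAS-BLED drug point is scored over the whole 5-year period, not the 3-month window used elsewhere for the same drugs, so untreated patients get a longer look-back than OAC starters

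*Protocol article*

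**What the plan says.** All references are to the protocol article.

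- **HAS-BLED, drugs or alcohol item:** "a point will be allocated where a patient receives a prescription for an antiplatelet or non-steroidal anti-inflammatory medication within the time period". The section Time periods defines three such periods, each 5 calendar years long (2003–2007, 2008–2012, 2013–2017).
- **Covariate classification, medication:** a drug counts as concomitant if at least one prescription was issued "in the 3 months prior to study entry, commencing an OAC, or the end of the time period". The list of drugs covered includes both HAS-BLED classes: "antihypertensives, antiplatelets, statins, diabetic medications, antiarrhythmics, non-steroidal anti-inflammatory drugs, corticosteroids" and others.
- **Covariate classification, comorbidities:** the plan counts those accrued by the index date in OAC starters and by the close of the period in untreated patients, using codes recorded "at any time prior to the relevant date for that period".
- **Source population:** "For the incidence calculations and comparison of patient characteristics, patients will be censored when they are prescribed an OAC". Objective 3 in the statistical analysis section repeats this censoring.
- **Objective 3:** mean HAS-BLED is a reported output for each period.
- **Renal impairment (a separate covariate):** "The Read code or test result dated closest to the relevant date for the period will be used to categorise the presence and level of" impairment. No direction in time is stated.

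**The concern.** Objective 3 compares patients who start an OAC with those who do not, to see which characteristics go with the prescribing decision. That requires each characteristic to be measured before the decision, over a window that does not depend on which group the patient ends up in.

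The 3-month medication rule meets this requirement: it has the same length in every group and ends at a reference date. The comorbidity rule looks back over the whole record, so it is not cut off at the start of a period either. The HAS-BLED drug point does neither. Its window starts with the period, or at later entry, and its end depends on treatment status.

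Two readings are possible:

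1. **Censoring at the index OAC applies.** A starter's window ends at the index date, while an untreated patient's can run to the end of the period. Untreated patients have more time in which to collect the point.
2. **The wording is taken literally.** A starter's window continues past the index date and includes prescriptions that cannot have influenced the decision.

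The comparison at stake is mean HAS-BLED in OAC starters and untreated patients. Under the first reading, untreated patients would look at higher bleeding risk than starters even if prescribing in the two groups were identical. A reader could take that as evidence that prescribers withhold OACs because of bleeding risk. Covariates found important in objective 3 also feed the Cox model in objective 4.

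**Working it through.** The documents state no figure for this point, so there is nothing to reproduce. The check is a comparison of the rules, followed by an illustration under stated assumptions.

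**Rules side by side**

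| Item | Window | Ends at |
|---|---|---|
| Antiplatelet or NSAID as concomitant medication | 3 months | study entry, OAC start or period end |
| Antiplatelet or NSAID as HAS-BLED point | the time period, up to 5 years | not stated; index OAC if censoring applies |

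**Inputs**

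- Period length: 5 years (Time periods).
- Short window: 0.25 years (Covariate classification).
- Rate *r* of new antiplatelet or NSAID prescriptions: assumed at 0.05, 0.10 and 0.20 per year, constant and equal in both groups.
- Population: patients with no current prescription, present for the whole period.
- Index dates of starters: assumed uniform over the 5 years.

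**Formulas**, for the probability of at least one prescription:

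- Untreated, full period: 1 − exp(−5*r*)
- Starters, period start to index: 1 − [1 − exp(−5*r*)]/(5*r*)
- Either group, 3-month window: 1 − exp(−0.25*r*)

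The item is worth one point, so the difference in probability is the difference in mean score.

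| *r* per year | Untreated | Starters | Gap in mean HAS-BLED | 3-month window, both groups |
|---|---|---|---|---|
| 0.05 | 0.221 | 0.115 | 0.106 | 0.012 |
| 0.10 | 0.393 | 0.213 | 0.180 | 0.025 |
| 0.20 | 0.632 | 0.368 | 0.264 | 0.049 |

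For *r* = 0.10: 1 − exp(−0.5) = 0.393; 1 − 0.393/0.5 = 0.213; the gap is 0.180. With the 3-month window the gap is zero by construction.

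**Sensitivity to the index date.** With every index date at mid-period (2.5 years), the gap is exp(−2.5*r*) − exp(−5*r*), which is 0.10, 0.17 and 0.24 for the three rates.

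**Dilution by current users.** A patient already on one of these drugs scores under either window and adds nothing to the gap. If a share *s* of each group is already treated, the gap becomes (1 − *s*) times the figure above. The documents give no value for *s*. With *s* assumed at 30% or 60% and *r* = 0.10, it is 0.7 × 0.180 = 0.13 or 0.4 × 0.180 = 0.07. Later entry or earlier exit shortens the windows and reduces it further.

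**The case against.** The strongest reply is that the censoring rule already protects the comparison. Source population and Objective 3 both stop the clock at the index OAC, and Covariate classification makes the index date the reference point for OAC users. Read together, these keep post-index prescriptions out. That stands, and it makes unequal look-back the more likely harm. It does not remove the problem, because this censoring is what shortens the starters' window.

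A reader might infer that post-initiation data and unequal windows operate together. For a patient present throughout the period they are alternatives: censoring excludes later prescriptions, and without censoring both groups have the same 5 years.

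A reader might also infer that the renal rule uses post-index tests and contradicts the comorbidity rule. The documents do not support this. The rule only lacks a direction, and the comorbidity wording and the censoring suggest that earlier records are meant. It also governs the stand-alone renal covariate; the renal item of HAS-BLED has its own definition, which does not use the closest record. A gap in the wording remains for untreated patients, who can stay under follow-up into the next period, so their closest record could fall after the reference date.

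Nor would the results necessarily show the same drug at two frequencies: Objective 3 plans only the mean score, not its components.

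Finally, the HAS-BLED elements were adapted to CPRD data, so a different window may be deliberate, and the Discussion says most of the medications are for chronic conditions, so the two windows may often pick out the same people. Both remarks bear on size. Neither gives a reason for a window whose length depends on treatment group, and the Discussion defends only the 3-month rule.

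**Conclusion.** The point holds for the HAS-BLED drug item. Its period-long window conflicts with the 3-month rule for the same drugs. Under the plan's own censoring, it favours a higher mean HAS-BLED in untreated patients for reasons unrelated to bleeding risk. If censoring is not applied to the item, the defect is post-decision data instead.

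The artificial gap is about 0.11 to 0.26 points at assumed rates of 5% to 20% per year. These figures rest on equal constant rates, uniform index dates, presence for the full period and no current prescription. They should not be read as the gap to expect between the full groups, which would be smaller by the share already on these drugs and by incomplete follow-up within the period.

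One item of the score is affected. The stated maximum of 8 (1 + 2 + 1 + 1 + 1 + 2) is unaffected. The renal wording needs clarification and is not an error.

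**What to change.** Define the HAS-BLED drug point as at least one antiplatelet or NSAID prescription in the 3 months before the OAC index date or, for no-OAC patients, before the end of the time period. This is the medication rule already in Covariate classification, applied identically to all groups.

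The cost is one change of wording, and the medication variable already planned can be reused. The small downside is that intermittent users with no prescription in those 3 months are not scored.

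As a minor clarification, state that the renal covariate uses the latest code or laboratory result dated on or before the reference date. A few patients whose only renal record is later would then count as not recorded.
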